## Abstract

**Background:**

Too little sleep and the consequences thereof are a heavy burden in modern societies. In contrast to alcohol or illicit drug use, there are no quick roadside or workplace tests for objective biomarkers for sleepiness. We hypothesize that changes in physiological functions (such as sleep–wake regulation) are reflected in changes of endogenous metabolism and should therefore be detectable as a change in metabolic profiles. This study will allow for creating a reliable and objective panel of candidate biomarkers being indicative for sleepiness and its behavioral outcomes.

**Methods:**

This is a monocentric, controlled, randomized, crossover, clinical study to detect potential biomarkers. Each of the anticipated 24 participants will be allocated in randomized order to each of the three study arms (control, sleep restriction, and sleep deprivation). These only differ in the amount of hours slept per night. In the control condition, participants will adhere to a 16/8 h wake/sleep regime. In both sleep restriction and sleep deprivation conditions, participants will accumulate a total sleep deficit of 8 h, achieved by different wake/sleep regimes that simulate real-life scenarios. The primary outcome is changes in the metabolic profile (i.e., metabolome) in oral fluid. Secondary outcome measures will include driving performance, psychomotor vigilance test, d2 Test of Attention, visual attention test, subjective (situational) sleepiness, electroencephalographic changes, behavioral markers of sleepiness, changes in metabolite concentrations in exhaled breath and finger sweat, and correlation of metabolic changes among biological matrices.

**Discussion:**

This is the first trial of its kind that investigates complete metabolic profiles combined with performance monitoring in humans over a multi-day period involving different sleep–wake schedules. Hereby, we aim to establish a candidate biomarker panel being indicative for sleepiness and its behavioral outcomes. To date, there are no robust and easily accessible biomarkers for the detection of sleepiness, even though the vast damage on society is well known. Thus, our findings will be of high value for many related disciplines.

**Trial registration:**

ClinicalTrials.gov Identifier NCT05585515, released on 18.10.2022; Swiss National Clinical Trial Portal SNCTP000005089, registered on 12 August 2022.

## Administrative information

Note: the numbers in curly brackets in this protocol refer to SPIRIT checklist item numbers. The order of the items has been modified to group similar items (see http://www.equator-network.org/reporting-guidelines/spirit-2013-statement-defining-standard-protocol-items-for-clinical-trials/).

## Introduction

### Background and rationale {6a}

Too little sleep and the consequences thereof are a heavy burden in modern societies. Estimating that people sleep on average up to 2 h less over the last decades, sleepiness needs to be considered as a significant societal problem of our modern world [1, 2]. The Swiss Federal Roads Office (FEDRO) states that overtiredness and microsleep are among the top 5 main causes of motorway accidents leading to injuries between 2017 and 2021 [3]. In addition, the Swiss Council for Accident Prevention estimates that drowsy drivers cause 10–20% of all driving accidents [4]. Young males and shift workers seem to be prevalently affected here [5, 6]. The Swiss National Accident Insurance Fund (Suva) estimates that 53,000 occupational accidents per year are sleep-related, producing costs of 283 million Swiss francs [7].

In contrast to alcohol or illicit drug use, there are no quick roadside or workplace tests for objective biomarkers for sleepiness. High inter-individual variability and subjective misinterpretations of sleepiness and sleep propensity provide a challenge to the development of objective sleepiness markers [8–10]. Although numerous different scales to assess sleepiness from different clinical perspectives do exist (for example, Karolinska Sleepiness Scale, Stanford Sleepiness Scale, Epworth Sleepiness Scale, and Johns Scale of Drowsiness), none of them can contain and evaluate all forms of sleepiness at once and therefore no gold standard exists [11]. Hence, objective and quantifiable biomarkers of acute sleepiness are urgently needed, not only for post hoc analysis but also for prevention.

### Objectives {7}

The main objective is built on the central hypothesis of biomarker discovery in metabolomics: Changes in physiological functions (such as sleep–wake regulation) are reflected in changes of endogenous metabolism and should therefore be detectable as change in metabolic profiles. Virtually all aspects of sleep–wake regulation are, at least in part, genetically determined and therefore, must have a molecular substrate. We hypothesize that increasing sleep drive or impaired wakefulness can be assessed by qualitative or quantitative fluctuations of certain metabolites in biological specimens, e.g., by accumulation or decrease of endogenous substances related to sleep propensity. Furthermore, a connection between metabolic profiling and sleepiness-induced performance impairment (especially the ability to drive) has never been drawn before. This study will allow for creating a reliable and objective panel of candidate biomarkers being indicative for sleepiness and its behavioral outcomes.

To avoid the limitations of previous studies, we paid special attention to taking into account specific aspects of human sleep–wake physiology in the study design, as well as the basics and subtleties of biological specimen sampling [12]. Oral fluid has proven its massive potential in metabolomics studies. Being an easily accessible and non-invasive biological fluid suitable for roadside or workplace testing, it overcomes the disadvantage of delay between the time of incident and time of sampling when relying on blood. It is therefore our matrix of choice for the systematic profiling of metabolites across all study blocks. Other alternative specimens such as finger sweat, exhaled breath, and dried blood spots will also be collected. All samples can be analyzed with standard forensic laboratory equipment (i.e., LC–MS).

### Trial design {8}

This is an exploratory, monocentric, controlled, randomized, crossover, clinical study to detect potential biomarkers. Each participant will be allocated in randomized order to each of the three study arms (control, sleep restriction, and sleep deprivation). Due to the nature of the study, blinding is not possible among participants and study personnel. Test assessors will be blinded, however.

## Methods: participants, interventions, and outcomes

### Study setting {9}

This monocentric study will be performed solely on the premises of the University of Zurich, Zurich, Switzerland.

### Eligibility criteria {10}

Previous studies revealed that salivary metabolite profiles are (to a different degree) biased by sex, age, body mass index (BMI), oral hygiene, oral conditions, diet, medication, and lifestyle habits like smoking or alcohol consumption [13, 14]. To control for these and possible sleep–wake-related confounding factors, candidate participants will need to fulfill the following.

Inclusion criteria:Male sexAge between 20 and 35 yearsUnderstanding and spoken command of the German languageGood health conditionBMI between 18.5–24.9 kg/m^2^Habitual average sleep duration between 7 and 9 h/nightHabitual consumption of 3 or fewer caffeinated beverages/dayHabitual consumption of 5 or fewer alcoholic beverages/weekGood sleep quality: Pittsburgh Sleep Quality Index score ≤ 5Reasonable oral hygiene (≥ 1 tooth brushing/day)Normal or corrected-to-normal visionCar driving license holder since at least 2 years (obtained in a country with right-hand traffic) and regular driver (≥ 1 per week)

Exclusion criteria:Two or more time zone crossings in the last 3 monthsHabitual napperHistory or presence of neurological disorder, psychiatric disorder, cardiovascular disorder, dental disorder, or any disorder that could pose a risk in participating or that could possibly influence study measurementsHistory or presence of a sleep disorder (screening night)Use of illicit drugs (urinary drug screening)Use of current medication (urinary drug screening) known to influence study measurementsExtreme chronotype (reduced Morningness-Eveningness-Questionnaire score ≤ 7 or ≥ 22)Current smokerHabitual use of energy drinks (> 1/week)Severe skin allergies or hypersensitivitiesFood allergiesHospital stay in the past 6 monthsShift worker, night workerRecent past (last 3 months) or present COVID-19 infectionFainting at the sight of blood or needlesParticipation in a clinical study less than 30 days ago or is currently participating in other clinical studiesSimulator sickness syndromeRefusal to sign informed consent

### Who will take informed consent? {26a}

Study personnel obtain written informed consent from potential trial participants prior to any study measure.

### Additional consent provisions for collection and use of participant data and biological specimens {26b}

If not yet covered in this study’s informed consent form, a signed consent must be obtained from every participant in ancillary studies.

## Interventions

### Explanation for the choice of comparators {6b}

Two sleep deficit interventions (sleep deprivation and sleep restriction) were designed to simulate highly prevalent real-life sleep scenarios. Whereas all-night sleep deprivation mimics a night shift work or going out, the sleep restriction regime mimes a typical workweek schedule with an equal total sleep loss than all-night sleep deprivation. Cumulative effects of sleep restriction leading to performance impairment and increased crash risk have been described before**,** but their impact on metabolic outcomes is unknown [10, 15, 16].

While a constant routine protocol (e.g., permanent dim light conditions, strictly controlled body posture) is necessary to avoid masking in circadian studies, a slightly reduced level of control is deemed sufficient in the present study focused on sleep–wake rather than circadian perturbation.

### Intervention description {11a}

Three conditions that only differ in the amount of hours slept per night will be studied (see Fig. 1).

**Fig. 1 Fig1:**
[figure not shown]
Overview of sleep regime in different study arms (control, sleep deprivation, sleep restriction). Yellow colors indicate time awake, gray colors bed times, vertical lines a period of 24 h. For further explanations, see the text. Abbreviations: SD, sleep deprivation; SR, sleep restriction

In the control (C) condition, participants will adhere to a 16/8-h wake/sleep regime for 3 consecutive days at home and for the following 2 days in the sleep laboratory under the supervision of study personnel.

In the sleep deprivation (SD) condition, participants will follow a 16/8-h wake/sleep regime for 3 consecutive days at home and one night of supervised sleep deprivation (24/0 h) in the sleep laboratory, thus generating a total sleep deficit of 8 h compared to the control condition. The following night (recovery night) offers 8 h of supervised sleep.

In the sleep restriction (SR) condition, participants will follow an 18/6-h wake/sleep regime for 3 consecutive days at home and 1 day in a sleep laboratory under the supervision of study personnel, thus also accumulating a total sleep deficit of 8 h compared to the control condition. The following night (recovery night) offers 8 h of supervised sleep.

### Criteria for discontinuing or modifying allocated interventions {11b}

Discontinuation or modification of allocated interventions is not planned. Discontinuation is possible in case of adverse events or if participants do not adhere to protocol requirements. In addition, if organizational or the participant’s situation require, a switch between pre-scheduled control and sleep deprivation conditions may be allocated at the participant’s arrival in the sleep laboratory. These two conditions only differ in the amount of scheduled sleep in the subsequent night. The modification in the allocated conditions may permit the efficient usage of resources, and thus reduce the total trial duration and facilitate intra-individual comparability of study specimens if collected in shorter time intervals.

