## Assignment of interventions: allocation

### Sequence generation {16a}

The order of interventions will be defined by random envelope picking of participants after successful passing of screening tests. Given three study arms (C, SD, SR), there are six different possible orders of interventions. Each order will be performed four times in an equal ratio. The first 18 participants will pick their respective assignment envelope from box A which contains all possible orders in triplicates (3:3:3:3:3:3), thus guaranteeing an equal allocation ratio until the minimum sample size is reached. The remaining participants will draw from box B, where each order is contained once (1:1:1:1:1:1).

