## Assignment of interventions: blinding

### Who will be blinded {17a}

Due to the nature of the study interventions, neither participants nor study personnel can be blinded. To ensure an unbiased rating of participants, outcome assessors of respective performance tests will be blinded.

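### Control and sleep deprivation may be switched at arrival because of the participant's situation, so the condition can depend on his state that day and the four-per-order balance can fail

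*Protocol article*

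**What the plan says.** Section {11b} opens with "Discontinuation or modification of allocated interventions is not planned". It then provides that "a switch between pre-scheduled control and sleep deprivation conditions may be allocated" when the man reaches the sleep laboratory, the condition being "if organizational or the participant’s situation require". Two reasons are offered. One is that "These two conditions only differ in the amount of scheduled sleep in the subsequent night". The other is practical: "The modification in the allocated conditions may permit the efficient usage of resources, and thus reduce the total trial duration", together with shorter intervals between a man's samples.

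Section {16a} randomises the order of the three conditions by envelope after screening and states "Each order will be performed four times in an equal ratio". Section {18b} books the sessions directly after screening. Section {17a} says that "neither participants nor study personnel can be blinded"; only the assessors of the performance tests are. Section {20b} plans no adjusted analyses unless incomplete datasets disturb the balance between conditions.

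The article gives no criteria for the participant's situation, no decision-maker, no limit on the number of switches and no rule for analysing switched sessions.

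**The concern.** Randomising the order makes a man's state on a given day independent of the condition he receives that day. A switch decided at arrival, on grounds that may include how he is, removes that independence. The trial studies sleepiness, so a man who arrives tired is a plausible candidate for a switch, and tiredness is what the candidate biomarkers should track.

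The opportunity is one-sided within a man. If each condition is given once, a switch is possible only at the first of his control and sleep deprivation sessions. Selection on that visit's state is not offset at the other visit.

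The contrast at stake resembles the one behind the sample size in {14}, where prolonged wakefulness was compared with a control condition that included sleep. A switched man has complete data, so the exception in {20b} for incomplete datasets would not prompt an adjusted analysis.

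**Working it through.** **1. The plan's own allocation figure.** Three conditions give 3! = 6 orders. Box A holds 6 × 3 = 18 envelopes and box B 6 × 1 = 6. The total is 24 = 6 × 4, so {16a} reproduces. Control precedes sleep deprivation in three of the six orders, which is 12 men; the other 12 have the reverse.

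**2. Effect of switches on balance.** Each switch in one direction moves one man. The 12:12 split becomes 13:11 after one switch, 14:10 after two and 16:8 after four. Four per order then fails unless switches happen to offset each other.

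**3. Hypothetical bias in arrival state.** Assumptions, none from the documents:
- arrival state is standard normal and independent at the two visits (unit: one visit standard deviation; higher is worse);
- half the men are due for sleep deprivation first;
- of these, the worst fraction q at the first visit are moved to control;
- no other switches occur.

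With z the upper-q normal quantile and φ the normal density, the mean difference in arrival state (control minus sleep deprivation) is:
- control-first men: 0;
- switched men: φ(z)/q, with share q of the sleep-deprivation-first men;
- unswitched sleep-deprivation-first men: φ(z)/(1 − q), with share 1 − q.

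The sleep-deprivation-first half averages φ(z) + φ(z) = 2φ(z), so all men together average φ(z).
- q = 0.25 (0.25 × 12 = 3 men): φ(0.674) = 0.318. Simulation gave 0.316.
- q = 0.10 (0.10 × 12 = 1.2 men): φ(1.282) = 0.175. Simulation gave 0.173.

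**4. Scale.** Section {14} gives no effect size, standard deviation or sidedness. Solving the paired t-test for n = 17, alpha 5% and power 80% gives a standardised paired difference (dz) of 0.724 two-sided, or 0.63 one-sided. If arrival state is all of the within-man variation and carries fully into the outcome, the difference has standard deviation √2:
- q = 0.25: 0.318 / (1.414 × 0.724) = 31% (36% with 0.63);
- q = 0.10: 0.175 / (1.414 × 0.724) = 17% (20% with 0.63).

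If half of arrival state carries over, these figures halve.

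**5. Under no true effect** (n = 24, 4,000 simulated trials, arrival state explaining 25% to 100% of within-man variance):

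| Switches | Bias (visit standard deviations) | Type I error |
|---|---|---|
| none | about 0 | about 5% |
| about 1 (q = 0.10) | 0.08 to 0.18 | 5% to 9% |
| about 3 (q = 0.25) | 0.16 to 0.32 | 8% to 19% |

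**6. Does leaving out switched men help?** Only partly. The unswitched sleep-deprivation-first men are selected for good arrival states. The remaining bias is 0.5φ(z)/(1 − 0.5q) = φ(z)/(2 − q): 0.318/1.75 = 0.18 for q = 0.25 and 0.175/1.90 = 0.09 for q = 0.10.

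**7. Does analysis by the order drawn help?** The drawn order is independent of arrival state, so this bias vanishes. The price is dilution. If a share p of men is switched, the contrast is multiplied by (1 − p) − p = 1 − 2p; for 3 of 24 that is 1 − 2 × 0.125 = 0.75.

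**The case against.** The protocol's defence is that control and sleep deprivation share the same home schedule and differ only in the coming night. That shows a switch is feasible. It does not make the choice independent of the participant's state.

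Several points on the other side stand:
- Other rules narrow or record arrival state. Adherence to the home sleep regime is checked by actigraphy and diary ({11c}), and outcome data are excluded after deviations from it ({18b}). A man who needs medical care or starts medication falls under {11d}. Oral fluid, vigilance, attention and sleepiness scales are taken at 6 pm on arrival ({12}). No adjustment for that baseline is specified, so this mitigates the problem without curing it.
- The stated purposes are mostly logistical. Switches unrelated to the man's state disturb the order balance but do not cause this bias.
- The trial is exploratory ({8}), and sleep restriction is untouched.

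A reader might infer more than the article supports. The concealed draw is not undone: the envelopes conceal the order until it is picked, and each man should still receive both conditions. That unblinded staff decide the switch is an inference, since no decision-maker is named. A bias toward no difference is not established. It requires switches from sleep deprivation to control and features that move with tiredness as they do with deprivation; switches of tired men the other way would reverse the sign.

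**Conclusion.** The point holds as a defect in the rule. As written, {11b} lets the condition depend on the participant's state that day, conflicts with its own first sentence, and allows departures from the balance stated in {16a}. Nothing else in the article limits or offsets the switch.

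The size and direction of any bias are unknown because no switch rate is given. The 31% and 17% are hypothetical upper values for the two assumed switch rates. They require every switch to be driven by the man's state, every switch to run from sleep deprivation to control, and full carry-over into the outcome. The effect of 0.72 is an inference from n = 17 (two-sided) and should not be read as a planned value.

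**What to change.** - Reconcile {11b} with {16a} and with its own opening sentence.
- Remove the participant's situation as a ground for switching conditions. Allow only organisational switches that are decided and recorded before he is seen.
- Log every switch with time, reason and decision-maker.
- Analyse by the condition and period actually carried out. Add a sensitivity analysis of sleep deprivation versus control by the order drawn, reported with the number switched so that the dilution can be judged. Adjustment for the 6 pm arrival baseline is a useful option and would need a matching sentence in {20b}. Excluding switched men should not be relied on, since it leaves about half of the bias.

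How to handle a session that a participant cannot undergo as scheduled is for the sponsor to reconcile with {11d}.

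The cost is a short amendment, a log and a little scheduling flexibility. No extra participants or samples are needed.

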### Strategies to improve adherence to interventions {11c}

Participants’ adherence to sleep regimes will be monitored by the use of wrist actigraphy and sleep–wake diaries. At the time of arrival at the sleep laboratory, a urine sample will be collected and tested for recent drug use, as well as a breath test to detect recent alcohol consumption. Once at the sleep laboratory, participants will be under constant supervision of study personnel.

### Relevant concomitant care permitted or prohibited during the trial {11d}

Medical care will be available throughout the study. If participants need to seek medical care during the trial period or start taking medication, the principal investigator will decide whether the participant will have to be excluded or whether the study can be completed after completed recovery.

### Provisions for post-trial care {30}

A general follow-up appointment is not foreseen. Participants who withdraw from the study due to adverse events will undergo a follow-up check up to 30 days after exclusion. Compensation to those who suffer harm from trial participation will be paid according to policy conditions concluded by the University of Zurich and the respective insurance company.

### Outcomes {12}

The primary outcome of this trial is changes in the metabolic profile (i.e., metabolome) in oral fluid. Investigators will collect samples from participants for quantification of all detectable metabolites after arrival at the study site (6 pm, baseline), repeatedly during scheduled wakefulness (8 am, 12 pm, 4 pm, 7 pm, 11 pm), and in the morning after recovery night (8 am). They will analyze which metabolite concentration values undergo significant changes during sleep deficit conditions in comparison to the control condition and also show the effects of recovery sleep. These will serve as candidate biomarkers.

Secondary outcome measures will include:i.Driving performance: Investigators will gather driving simulation results via Standardized Application for Fitness to Drive Evaluations (S.A.F.E.) [17–19], and analyze their changes after sleep deficit in comparison to the control condition. Driving simulation test is scheduled once per study arm, in the morning after the experimental night (10 am).ii.Psychomotor vigilance test (PVT) [20]: The PVT is a gold standard reaction time test to assess vigilance and sustained attention. It will be performed after arrival at the study site (6 pm, baseline), repeatedly during scheduled wakefulness (8 am, 12 pm, 4 pm, 7 pm, 11 pm), and in the morning after recovery night (8 am).iii.d2 Test of Attention [21, 22]: The d2 Test of Attention is a paper and pencil test to assess selective and sustained attention and visual scanning speed. It is scheduled after arrival at the study site (6 pm, baseline), repeatedly during scheduled wakefulness (8 am, 12 pm, 4 pm, 7 pm, 11 pm), and in the morning after recovery night (8 am).iv.Visual attention test [23]: The visual attention test is a virtual reality glasses test to assess visual skills in a complex visual environment. It will be conducted after arrival at the study site (8 pm, baseline), repeatedly during scheduled wakefulness (10 am, 2 pm, 6 pm, 8 pm), and in the morning after recovery night (8 am).v.Subjective situational sleepiness: Participants will complete the Karolinska Sleepiness Scale (KSS) [24] questionnaire after arrival at the study site (6 pm, baseline), repeatedly during scheduled wakefulness (8 am, 12 pm, 4 pm, 7 pm, 11 pm), and in the morning after recovery night (8 am).vi.Subjective sleepiness: Participants will complete the Stanford Sleepiness Scale (SSS) [25] questionnaire after arrival at the study site (6 pm, baseline), repeatedly during scheduled wakefulness (8 am, 12 pm, 4 pm, 7 pm, 11 pm), and in the morning after recovery night (8 am).vii.Electroencephalographic (EEG) changes: Investigators will analyze changes in sleep and wake EEG patterns of participants by calculating sleep scores according to the American Academy of Sleep Medicine (AASM) scoring manual [26]. EEG recordings will be performed during scheduled sleep, driving simulation test (10 am), and at two time points during scheduled wakefulness (12 pm, 7 pm).viii.Behavioral markers of drowsy driving: Investigators will examine participants immediately after the driving simulation test for behavioral abnormalities concerning orientation, coordination, speech, mood, appearance, reaction, and pupillary light reflex.ix.Changes in metabolite concentrations in exhaled breath: Investigators will collect exhaled breath samples from participants for quantification of all detectable metabolites after arrival at the study site (8 pm, baseline), repeatedly during scheduled wakefulness (10 am, 2 pm, 6 pm, 8 pm, 11 pm), and in the morning after recovery night (8 am). They will analyze which metabolite concentration values undergo significant changes during sleep deficit conditions sessions in comparison to the control condition and also show the effects of recovery sleep. These will serve as secondary candidate biomarkers.x.Changes in metabolite concentrations in finger sweat: Investigators will collect finger sweat samples from participants for quantification of all detectable metabolites after arrival at the study site (8 pm, baseline), repeatedly during scheduled wakefulness (10 am, 2 pm, 6 pm, 8 pm, 11 pm), and in the morning after recovery night (8 am). They will analyze which metabolite concentration values undergo significant changes during sleep deficit conditions sessions in comparison to the control condition and also show the effects of recovery sleep. These will serve as secondary candidate biomarkers.xi.Correlation of metabolic changes between blood and non-invasive specimens: Investigators will compare metabolite concentrations in non-invasive matrices (oral fluid, finger sweat, exhaled breath, and dried blood spots) and compare those with a blood sample. The collection of specimens for this outcome is scheduled immediately after the driving simulation test in each study arm.
